## Statistical methods

### Statistical methods for primary and secondary outcomes {20a}

Our data analysis plan will involve descriptive statistics, visualizations, and models of change over time. We will follow an intent-to-treat approach [41], analyzing all the study participants assigned to their intervention arm. Our findings will be summarized using tables and graphs.

For descriptive statistics, we will compute the frequencies and percentages of the demographic and clinical characteristics for the study participants at baseline by the intervention arm. To test for significant group differences in the sample characteristic variables, we will use *F*, *t*, and *χ*^2^ statistics [42].

Primary outcome variations across all the time points will be visualized using multiple plots. We will include line plots for depressive symptoms, anxiety symptoms, academic grades, well-being, and perceived social support for the Shamiri intervention per implementer and TAU control arm, visualizing scores before, during, and after the intervention and control condition.

We will build linear mixed effects models [43, 44] as part of the analysis to compare the outcomes of the two Shamiri intervention and the TAU control groups. These models will consider the hierarchical nature of the data, where participants are nested within organizational structures (participant in lay provider/group in school in county). The standard models will be random-intercept models; we will also test the inclusion of random slopes for individual differences. Some of the model elements (e.g., multiple levels of nesting and the random slope) may result in models that are too complex, unidentifiable, or overfit; in such a case, more parsimonious models will be selected.

The arm, time, and interaction between these two will be included in all the models as fixed effects. Other variables that will be included either in a fixed effect or in a random effect specification in the models are age, gender, lay provider, lay provider gender, school, and county. Baseline scores may also be included. Age will be included as a covariate as older adolescents in Kenya have been found to on average have increased psychosocial stress compared to younger adolescents which may heighten depressive and anxiety symptoms [12].

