Gender will be included because Kenyan adolescents have shown gender differences in internalizing problems [8, 12]. Female adolescents have previously reported higher anxiety and depression symptoms as compared to males. Past studies [8, 12] have shown that adolescents in lower-resource schools report higher depression and anxiety symptoms. Lastly, we will include details of lay providers like gender because we would like to explore if the gender of a lay provider affects the study participants.

A *p*-value less than 0.05 in the interaction between the time variable and the arm variable will be considered statistically significant. If the interaction is significant, we will look at the conditional mean difference between the arms at each time point from end point to follow-up. We will assess this and report marginal (predictive) means. If these differences are significant (*p* < 0.05) and the control has scores associated with less favorable outcomes, we will conclude there was improvement due to centralized or decentralized arm over time. If the interaction is not significant but the main effect of centralized or decentralized arm is, and the effect points to lower symptoms in the centralized or decentralized arms, we conclude there was improvement due to centralized or decentralized delivery.

Effect sizes (ESs) will be computed from the mean differences across the different time points for the arms. We will compare Cohen’s D for each outcome at baseline, midpoint, endpoint, and 1-month follow-up for the study participants in the Shamiri intervention arms and TAU control arm. Statistically significant Cohen’s *D* in the direction of less symptoms on average in the arms will reflect greater improvements for intervention compared to control.

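### The fallback rule concludes improvement from an arm main effect that can be, or contain, the pre-treatment baseline difference

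*Protocol article*

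**What the plan says.** All of this is in the Protocol article, Statistical methods for primary and secondary outcomes {20a}.

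- **Model.** "The arm, time, and interaction between these two will be included in all the models as fixed effects". On baseline it adds only that "Baseline scores may also be included". Participant timeline {13} places assessments at 0, 2, 4 and 8 weeks, so baseline is the first of four.
- **Rule 1.** A p-value "less than 0.05 in the interaction between the time variable and the arm variable will be considered statistically significant". If so, "we will look at the conditional mean difference between the arms at each time point from end point to follow-up". Benefit is concluded if those differences are significant "and the control has scores associated with less favorable outcomes".
- **Rule 2, the fallback.** "If the interaction is not significant but the main effect of centralized or decentralized arm is, and the effect points to lower symptoms" in the active arms, improvement due to that form of delivery is concluded.
- **Cohen's D.** It is compared "for each outcome at baseline, midpoint, endpoint, and 1-month follow-up", and a statistically significant value "in the direction of less symptoms on average in the arms will reflect greater improvements for intervention compared to control". This statement does not depend on the interaction test.

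The text does not rank these statements or give an error rate for them in combination.

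**The concern.** Rule 2 applies exactly when the trial has failed to show that the arms diverge over time. If baseline is a level of time, a persistent gap without divergence is what chance imbalance at randomisation produces. Calling that gap improvement due to the intervention credits something present before treatment began. The same term is also a poor measure of a real effect, because it includes a time point at which no effect is possible.

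Two further features add to this. The Cohen's D sentence uses the language of significance and improvement at several time points, baseline among them, so it can be taken as another way to claim benefit. And Rule 2 and the Cohen's D sentence express benefit as lower or fewer symptoms. Three of the five primary outcomes (MSPSS, SWEMWBS, academic performance) are not symptom scales and improve upwards.

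**Working it through.** **The plan's own figure.** The article states no false-positive rate. Its only related figure is in Sample size {14}: at least 80% power for an effect of 0.22 with 1554 participants, allowing 40% attrition. A simple check uses 1554 × 0.6 / 3 = 310.8 per arm. Then 0.22 × √(310.8/2) = 2.74, and 2.74 − 1.96 = 0.78, which gives 78.3% power. That is close to the stated 80%, so 0.22 is used below as the plan's effect size.

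**Inputs.** From the article: three equal arms (Sequence generation {16a}), four assessments, p < 0.05. Assumed, because the article does not give them: within-person correlation ρ from 0.3 to 0.7, normal outcomes, complete data, no clustering, two-sided tests with a direction condition (so 2.5% per arm-versus-TAU comparison), and Rule 1 met by endpoint or follow-up.

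**Step 1: what the main effect is.** Let d0, d1, d2, d3 be the arm-minus-TAU differences at baseline, midpoint, endpoint and follow-up.

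- Reference coding with baseline as reference: main effect = d0.
- Sum coding: main effect = (d0 + d1 + d2 + d3)/4.

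With a true effect of 0.22 at every post-baseline time, the expected main effect is 0 under reference coding and 0.22 × 3/4 = 0.165 under sum coding.

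**Step 2: how often imbalance triggers the fallback under no effect.** With equal correlation ρ between visits, d0 and the four-time average have correlation √((1 + 3ρ)/4), which is 0.69, 0.79 and 0.88 for ρ = 0.3, 0.5 and 0.7. Given a baseline z > 1.96, the bivariate normal probability that the average also exceeds 1.96 is 32%, 43% and 56%. Requiring in addition that the joint interaction test is not significant gives, by simulation (400,000 replicates), 30%, 40% and 52%. Under reference coding the main effect is d0 itself, so only the interaction condition can stop the rule. It fires in 85%, 88% and 91%, that is about 85–90%.

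**Step 3: overall false benefit per arm, one outcome** (400,000 replicates, categorical time, joint interaction test, sum coding unless stated):

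| Claims counted | ρ = 0.3 | ρ = 0.5 | ρ = 0.7 |
|---|---|---|---|
| Rule 1 alone | 0.72% | 0.58% | 0.40% |
| Rules 1 and 2 | 3.09% | 2.96% | 2.82% |
| Rules 1 and 2, reference coding | 2.86% | 2.81% | 2.72% |
| Rules 1, 2 and post-baseline D | 7.43% | 6.60% | 5.63% |
| Rules 1, 2 and D including baseline | 9.04% | 7.92% | 6.58% |

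Testing the interaction separately per arm raises the Rules 1 and 2 figure to at most 3.37% (ρ = 0.3). Across the variants, Rules 1 and 2 together lie at about 2.6–3.4%. With D counted, 5.63/2.5 = 2.3 and 9.04/2.5 = 3.6. Against 5% the same figures are 5.63/5 = 1.1 and 9.04/5 = 1.8.

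**Step 4: direction.** Rule 1 is neutral on direction (less favourable scores in control). Rule 2 and the Cohen's D sentence refer to symptoms. The three statements therefore do not use the same definition of benefit.

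**The case against.** **The error rate is not inflated by the fallback.** This stands. Rules 1 and 2 are mutually exclusive, and together they stay near 2.5%. A reader might infer from the several routes that false claims run at about three times nominal. The article does not support that as a headline. It needs the Cohen's D sentence to be a third decision rule and a 2.5% directional benchmark that the article does not state. The article uses the language of concluding only for the two model-based rules, and the D sentence can be read as describing size. Its reference to statistical significance permits the other reading but does not state it.

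**Baseline may not be an outcome time point.** If baseline is only a covariate and only post-baseline scores are modelled, a sum-coded main effect is a legitimate average treatment effect. This also stands, so the point is conditional. But the article leaves the choice open while fixing a conclusion rule that is valid under only one of the options.

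**The fallback can catch a real effect.** With a true effect of 0.22 at all post-baseline times and the stated attrition, the sum-coded fallback fires in about 14%, 5% and 0.3% of trials for ρ = 0.3, 0.5 and 0.7, against about 2.4% under no effect. So it is too strong to say that any firing is probably imbalance. With complete data the interaction is already significant in about 92% or more of such trials, so the fallback then adds little.

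**Wording and scope.** Lower symptoms is probably shorthand, and that part is minor. Grades are collected by school term, not at the four visits, so the simulated rates do not transfer to them directly.

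**Conclusion.** The concern holds as a validity defect in a stated decision rule. Unless baseline is removed as an outcome time point, the fallback can report pre-treatment imbalance as improvement, and it dilutes a true effect (0.22 becomes 0.165 under sum coding, or vanishes in expectation under reference coding). Given a chance favourable imbalance, it fires in about 30–52% of null trials under sum coding and about 85–90% under reference coding.

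It does not hold as a claim of a threefold error rate. The two model-based rules give about 2.6–3.4% false benefit per arm. If significant Cohen's D values are also used as claims, the rate is about 5.6–7.5% (post-baseline D) or 6.6–9.0% (baseline D included): 2.3–3.6 times 2.5%, or 1.1–1.8 times 5%. Nearly all of that rise comes from the D tests.

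The figures rest on the assumed correlation of 0.3–0.7, complete data and no clustering, for one outcome. Multiplicity over the five primary outcomes is not counted.

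**What to change.** 1. Delete the main-effect fallback. Alternatively, keep it but define it as the average arm-minus-TAU contrast over post-baseline times, with baseline as a covariate and not as an outcome level.
2. Rest the claim for each active arm and outcome on the model-based arm-minus-TAU contrasts at endpoint and follow-up, the time points the article already names, and state which one governs.
3. Report Cohen's D with a confidence interval as a descriptive size only, without a significance-based reading.
4. Replace the references to lower or fewer symptoms with the favourable direction for each scale.

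The cost is wording only: the contrasts come from the planned model and need no new data. The downside is fewer ways to reach a positive claim. A single prespecified contrast has a false-benefit rate of 2.5% per arm and about 4.6% for either arm on one outcome.

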### Interim analyses {21b}

N/A. We have no plans to conduct any analyses during the intervention sessions, as the sessions span only a 4-week period. Furthermore, we have not established any stopping guidelines as we expect no harm to the participants because of our study. However, if our tiered-model team comes across a participant who faces an elevated risk, the clinical network may choose to withdraw that participant from the study and offer more intensive clinical support instead. Refer to the supplementary emergency protocol for more details about the emergency protocol and risk assessment.

### Methods for additional analyses (e.g., subgroup analyses) {20b}

N/A. We do not have specific plans for any additional analyses based on subgroup or adjusted analyses besides the main analyses, though some may be conducted in an exploratory manner and reported as such. We do, however, plan to carry out moderator and mediator analyses which will not be part of the primary and secondary outcomes paper.

### Methods in analysis to handle protocol non-adherence and any statistical methods to handle missing data {20c}

We strive to reduce the percentage of missing data and limit attrition as much as possible. Should missing data, we will handle them statistically in the following way: missing data will be imputed five times using the multivariate imputation by chained equations (MICE) [44] algorithm with predictive mean matching in R; predictive mean matching appears to, at least in some cases, produce the least biased estimates and better model performance measures than other imputation methods [45].

As mentioned in the “Strategies to improve adherence to interventions {11c}” section, group sessions will be recorded and rated by trained independent evaluators. We plan to monitor these ratings in real time. In case systemic deviations from the protocol are identified in the sessions, the lay provider will be notified by the supervisor and asked to refer to the manual before the next session. Lay providers who deviate from the protocol will be continuously monitored in the next sessions. If any lay provider exhibits notable non-adherence to the protocol in more than three sessions, we may have to exclude the data associated with the students who would have been trained by these lay providers for sensitivity analysis.

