### Sample size {14}

We used the *simr* package in R to estimate the sample size needed for this trial. We used the lowest standardized effect size between the intervention and control we observed in a prior study [8] as our target effects, which was 0.22. Power simulations revealed that to detect an effect size of at least 0.22 at any time point with a significance level of *α* = 0.05 and a power of at least 80%, an effective sample size (i.e., including attrition of 40%) of 1554 participants is required. We expect up to 30% attrition at the midpoint and endpoint and up to 40% by follow-up based on our past trial [8], which is high. We rounded this up to 1600 participants required at baseline. For more details on our sample size determination and power analysis procedure, please see the supplementary materials.

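### Five imputations are too few for the 30–40% attrition the protocol expects: precision is lost, and p-values near 0.05 will depend on the random seed

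*Protocol article*

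**What the plan says.** Section {20c} of the protocol article states that "missing data will be imputed five times using the multivariate imputation by chained equations (MICE") "algorithm with predictive mean matching in R". The number of imputations is therefore fixed in this document. The predictors in the imputation model are not listed, and nothing is said about clustering in that model.

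Sample size {14} gives the expected loss: "up to 30% attrition at the midpoint and endpoint and up to 40% by follow-up based on our past trial". It sizes the trial on the smallest standardized effect of the earlier trial, "as our target effects, which was 0.22", with a significance level of "0.05 and a power of at least 80"%, and concludes that "an effective sample size (i.e., including attrition of 40%) of 1554 participants is required", rounded up to 1600.

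Section {20a} analyses the outcomes with linear mixed models in which "participants are nested within organizational structures": participant within lay provider or group, within school, within county. The decision rule there is p < 0.05, first for the arm-by-time interaction and then for the arm differences at the later time points.

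**The concern.** A multiply imputed estimate carries extra random error because m is finite. That error grows with the fraction of missing information (FMI) and shrinks with m. With little missing data, five imputations do little harm. Here the protocol itself allows for 30 to 40% loss and then applies a sharp threshold to each result. Two things are at stake. Some of the precision that 1600 students were recruited to provide is given away. And a conclusion near p = 0.05 may not be reproduced by someone who re-runs the code with another seed, which matters because the article promises public data and code.

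A second, conditional question is whether the imputation carries the same group structure as the mixed model fitted afterwards.

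**Working it through.** **Inputs from the protocol article.** m = 5 ({20c}); attrition up to 30% at midpoint and endpoint and up to 40% at follow-up ({14}); effect 0.22, alpha 0.05, power 80% ({14}); three equal arms, about 1600/3 = 533 per arm; groups of 10 to 15, each within one arm; threshold p < 0.05 ({20a}).

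**Assumptions.** Two-sided tests; FMI 0.3 to 0.4; correlation 0.6 between visits; group ICC 0 to 0.10.

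**The stated sample size (context only, not disputed).** The closed form 2(1.96 + 0.84)²/0.22² gives 325 per arm, 975 in three arms, and 975/0.6 = 1625 with 40% attrition, 4.6% above 1554. Power at 1600 with 40% attrition is 79.5%. The plan's figure comes from a mixed-model simulation whose inputs are in a supplement not at hand, so it is neither confirmed nor refuted.

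**Monte Carlo error.** The SD of the pooled estimate over seeds, in units of its standard error, is √(FMI/m).

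| FMI | m = 5 | m = 40 |
|---|---|---|
| 0.3 | √(0.3/5) = 0.245 | 0.087 |
| 0.4 | √(0.4/5) = 0.283 | 0.100 |

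**Width of the interval.** Rubin's degrees of freedom are about (m − 1)/FMI², and the widening is √(1 + FMI/m) × t(0.975, df)/1.96.
- FMI 0.3: df = 4/0.09 = 44; 1.030 × 2.015/1.96 = 1.06.
- FMI 0.4: df = 4/0.16 = 25; 1.039 × 2.060/1.96 = 1.09.

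**Power and type I error.** Simulating Rubin's rules with a test that would have 80% power at unlimited m gives about 75% (FMI 0.3) and 72% (FMI 0.4) at m = 5. At m = 40 it gives about 79 to 80%. Under the null, m = 5 rejects in 5.1 to 5.2% of trials.

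**Seed dependence.** Simulated follow-up contrast of two arms, each of 41 groups of 13 students; dropout 30% then 40%; predictive mean matching with 5 donors. ICC was 0.05 and FMI 0.30 in both example datasets. The table shows the 95% range of p over seeds.

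| Limiting p | m = 5 | m = 20 | m = 40 | m = 100 |
|---|---|---|---|---|
| 0.047 | 0.011–0.186 | 0.023–0.093 | 0.028–0.076 | 0.035–0.063 |
| 0.017 | 0.003–0.117 | 0.008–0.042 | 0.010–0.033 | 0.012–0.026 |

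For the second dataset 79% of seeds fall below 0.05 at m = 5, and practically all do at m = 40.

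**How often this matters.** At 80% power the expected z is about 2.80. With a Monte Carlo SD of about 0.26, a result within 1.645 × 0.26 = 0.43 of 1.96 changes sides in at least 5% of seeds. The chance that z falls between 1.53 and 2.39 is Φ(−0.41) − Φ(−1.27) = 0.341 − 0.102, or about 24%.

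**Conditional check on groups.** Same design with no true effect, 1500 replicates per ICC, m = 5; mean SE divided by empirical SE, with type I error in brackets.

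| Assumed ICC | Matching without a group term | Imputation with a group intercept |
|---|---|---|
| 0 | 1.03 (4.1%) | 1.04 (4.0%) |
| 0.02 | 0.91 (7.2%) | 0.96 (5.5%) |
| 0.05 | 0.89 (6.7%) | 0.98 (5.7%) |
| 0.10 | 0.82 (9.9%) | 0.92 (6.7%) |

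Raising m to 40 does not cure the column without a group term (0.92, 0.90 and 0.81 at ICC 0.02, 0.05 and 0.10).

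**The case against.** The strongest reply is that five imputations remain valid. Rubin's rules allow for finite m, type I error is close to nominal, and relative efficiency, 1/(1 + FMI/m), is 93 to 94%. Attrition is also not the same as missing information. The 40% is an upper bound at one visit, and earlier scores recover part of the loss. All of this stands. It is why the calculation uses a range of 0.3 to 0.4, and why the harm is described as lost precision and poor reproducibility. Results far from 0.05 will not move across it.

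A reader might go further and infer that the plan uses single-level imputation, ignores the groups and so understates the standard errors. The documents do not support that. They name predictive mean matching without saying which variant or which predictors are used. Such detail may sit in an analysis plan or supplement not at hand, and group or school could well be among the predictors. Even without a group term, earlier scores carry some of the group effect: the estimated ICC fell to about 40 to 50% of its complete-data value, not to zero. The ICCs are assumed, at ICC 0 nothing is understated, and at ICC 0.05 the difference in type I error (6.7% against 5.7%) is within simulation noise.

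**Conclusion.** The point holds for the number of imputations. Five is fixed in the text and is too few for the protocol's own expected attrition. With FMI of 0.3 to 0.4 it costs about 6 to 9% in interval width and about 5 to 8 points of an 80% power, and it leaves decisions near p = 0.05 dependent on the seed. It does not make the tests invalid. The seed ranges come from two example datasets and a single two-arm contrast at follow-up, not from the full arm-by-time model.

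The group level is a conditional remark only. The article does not say whether the imputation respects the nesting of the mixed model. If group is left out and the group ICC is above zero, standard errors would be about 9 to 18% too small at assumed ICCs of 0.02 to 0.10. Part of that shortfall (2 to 8%) also appears with group-aware imputation in the same simulation.

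**What to change.** In {20c}, replace five imputations with at least 40 to 50, and no fewer than the percentage of incomplete cases, and state the random seed in advance. A fixed seed alone makes the result repeatable but no less arbitrary; the larger m is what reduces the error. Even at m = 40 a limiting p of 0.047 still ranges from 0.028 to 0.076, so a result that close to the threshold should be reported with its Monte Carlo error or re-run with more imputations.

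In the same sentence, state that the imputation model includes the lay-provider or group level and keeps the arm-by-time structure, or point to the document that says so.

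The cost is computing time and a few lines of code. No new data are needed.
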